## Abstract

**Background:**

Pressure ulcers account for a substantial fraction of hospital-acquired pathology, with consequent morbidity and economic cost. Treatments are largely focused on preventing further injury, whereas interventions that facilitate healing remain limited. Intermittent electrical stimulation (IES) increases local blood flow and redistributes pressure from muscle-bone interfaces, thus potentially reducing ulcer progression and facilitating healing.

**Methods:**

The Pressure Injury Treatment by Intermittent Electrical Stimulation (PROTECT-2) trial will be a parallel-arm multicenter randomized trial to test the hypothesis that IES combined with routine care reduces sacral and ischial pressure injury over time compared to routine care alone. We plan to enroll 548 patients across various centers. Hospitalized patients with stage 1 or stage 2 sacral or ischial pressure injuries will be randomized to IES and routine care or routine care alone. Wound stage will be followed until death, discharge, or the development of an exclusion criteria for up to 3 months. The primary endpoint will be pressure injury score measured over time.

**Discussion:**

Sacral and ischial pressure injuries present a burden to hospitalized patients with both clinical and economic consequences. The PROTECT-2 trial will evaluate whether IES is an effective intervention and thus reduces progression of stage 1 and stage 2 sacral and ischial pressure injuries.

**Trial registration:**

ClinicalTrials.gov NCT05085288 Registered October 20, 2021.

**Supplementary Information:**

The online version contains supplementary material available at 10.1186/s13063-024-08085-x.

## Introduction

### Background and rationale

Pressure ulcers constitute a major morbidity in critically ill patients and are consequent to immobilization, deranged tissue perfusion, and poor nutrition all of which contribute to local tissue ischemia and skin and soft tissue breakdown through a reduction in perfusion pressure and impaired healing. The prevalence of pressure ulcers in ICU patients is 16–26% [1, 2]. In the United States, they are responsible for over 60,000 deaths each year, and the treatment of hospital-acquired pressure ulcers costs ~ $12 billion annually [3]. Despite preventive measures, pressure ulcers can develop within hours [4], especially in patients with hypotension, mechanical ventilation, renal replacement therapy, ICU sedation, and exposure to vasopressors [5]. Consequently, hospital-acquired pressure ulcers are about 4 times as common in ICUs than routine care wards [6].

Intermittent electrical stimulation (IES) was developed more than 35 years ago and was designed to increase tissue perfusion. The belief is that enhancing tissue perfusion improves local tissue oxygenation, improving tissue resistance to pressure and other factors that promote ulceration [7]. The contractions produced by IES reduce pressure around ischial tuberosities and distribute pressure to areas at lesser risk of breakdown from sustained loading (sitting or supine) as demonstrated by functional MRI [8]. The device invokes muscle contractions for 10 s every 10 min via surface electrodes, emulating the subconscious adjustments performed by able-bodied individuals in response to discomfort when seated or lying. Animal studies demonstrate that IES reduces internal pressure at bone-muscle interfaces (the hypothesized mechanism for injury development), increases tissue oxygenation in surrounding areas, and reduces or eliminates deep tissue injury in muscles subjected to prolonged loading [7, 9].

Clinical trials of IES have been limited to phase I trials which have demonstrated the safety of the device, ease of use, and patient satisfaction in multiple settings, including the ICU [10, 11]. Studies by Ahmetović et al. and Kane et al. evaluated the device as a preventive measure for pressure ulcers. No subjects in the trial groups developed a pressure ulcer.

Given the proposed mechanisms of IES and its performance in pilot and phase 1 trials, it is possibly that IES will prove an effective treatment for pressure injuries. Specifically, by preventing further injury through the offloading of pressure from bone-muscle interfaces and the increase of local blood flow, tissue that has already been injured may be less likely to progress to higher pressure stages and potentially heal more quickly. However, there is currently no pre-clinical or clinical evidence from adequately powered trials.

### Objectives

We designed the ‘Pressure Injury Treatment by Intermittent Electrical Stimulation (PROTECT-2) study to test the hypothesis that in patients with new or established stage 1–2 sacral and ischial pressure injuries, IES in addition to routine care for sacral and ischial pressure ulcers promotes healing over time better than routine care alone.

## Methods

### Trial design

PROTECT-2 is a parallel-group, unblinded multi-center randomized clinical trial that will assess whether IES combined with the standard of care (treatment) is superior to the standard of care alone (control). The trial is already IRB approved at all trial sites (US, Austria) and registered at ClinicalTrials.gov (NCT05085288). The SPIRIT checklist and figure for our proposal is provided in Fig. 1 and additional file 1. [12].

**Fig. 1 Fig1:**

Spirit Schedule of Enrollment, Interventions, and Assessments

### Trial population

We will include a minimum of 548 adult inpatients who meet the following criteria: (1) hospital inpatients, (2) new or established stage 1–2 sacral/ischial pressure injuries, (3) provide written informed consent in English. Consent is given by the patient or their legally authorized representative (LAR). Subjects enrolled via LAR will be themselves consented when able. Consent will be done in person or by telephone by investigators.

Patients with a pacemaker/AICD, active rhabdomyolysis, gluteal skin breakdown, and unstable fractures at risk of displacement by IES will be excluded. Patients with BMI > 40 kg/m^2^ will also be excluded based on concerns about not being able to elicit a reliable contraction of the muscle with the device. Patients with atrial or ventricular wires after cardiac surgery can be enrolled so long as they are not being actively paced or, in the opinion of the treating physician, likely to requiring pacing during the trial. Patients with multiple pressure injuries in higher stages can be enrolled as long as one of the sacral or ischial injuries is stage 1 or 2.

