### Randomization and blinding

Randomization sequences will be generated using the PLAN procedure in the SAS statistical software and will be stratified by clinical site and initial pressure injury stage at point of consent (stage I or II). Furthermore, random sized blocks will be used. Study personnel will randomize patients after enrollment via a central 24-h Interactive Web Randomization System (REDCap). This is an open label study, so no blinding is required. Randomization codes will be maintained until after all the data are collected and analyzed. The patient and study staff will be informed of the randomized allocation.

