#### Significance level

The significance level will be 0.05 for all hypothesis testing and will be controlled at 5% across any multiple comparisons using appropriate multiple testing procedures. Two-sided tests for superiority will be used throughout.

For the statistical analysis of clinical course, unstageable injuries will be assigned a score of 3 (equivalent to stage III injuries). If a patient experiences multiple sacral/ischial pressure injury simultaneously, the most severe injury will be used for analysis.

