#### Primary outcome

The primary outcome will be sacral and ischial pressure injury assessed with the SPI instrument score (range 0–4) over time. For the statistical analysis of clinical course, unstageable injuries will be assigned a score of 3 (equivalent to stage III injuries). For ulcers that progress to deep tissue injuries (DTI), these will be assigned a score of the previous ulcer stage plus one. If a patient experiences multiple sacral/ischial pressure injury simultaneously, the most severe injury will be used for analysis. The primary outcome will be based on the combined stage 1 and stage 2 ulcer types.

Patients will be assessed twice daily by the bedside nurse for pressure injury location and stage from study entry to discharge from the hospital or at least 30 days, whichever comes first. This is a standard wound care evaluation protocol for nursing. Wound care nursing specialist consultation staging will be used instead of bedside nursing staging should a discrepancy occur. If SPI scores are available after discharge and within the 30 days, those data will be included in the analyses as well, even if the SPI are healed or at the worst stage.

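### Patients with a co-existing higher-stage sacral or ischial injury may enrol on a stage 1–2 injury, but while the other injury is worse it, not the qualifying injury, sets the primary score

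*Protocol article*

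**What the plan says.** All references are to the protocol article.

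- **Trial population.** The inclusion criterion is "new or established stage 1–2 sacral/ischial pressure injuries". The next paragraph adds: "Patients with multiple pressure injuries in higher stages can be enrolled as long as one of the sacral or ischial injuries is stage 1"; a stage 2 injury suffices as well.
- **Primary outcome.** The score runs from 0 to 4 and is assessed twice daily. "If a patient experiences multiple sacral/ischial pressure injury simultaneously, the most severe injury will be used for analysis". The Significance level section repeats the rule: "the most severe injury will be used for analysis".
- **Objectives.** The hypothesis concerns IES "in patients with new or established stage 1–2 sacral and ischial pressure injuries".
- **Randomization and blinding.** Allocation is "stratified by clinical site and initial pressure injury stage at point of consent (stage I or II"). There is no third level.
- **Sample size considerations.** The target effect is Table 1 (A), for starting stages I and II combined. Table 1 (B) and (C) describe patients starting at stage I and at stage II.

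No sentence exempts an injury that was already above stage 2 at consent from the worst-injury rule, and none ties the score to the injury that made the patient eligible.

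**The concern.** Each rule is reasonable alone, but together they do not fit. Take a patient with a stage IV sacral and a stage 1 ischial injury. The patient is eligible on the ischial injury, can only be randomized as stage I or II, and is scored 4 at the first assessment. If the ischial injury heals, the score does not move. If the ischial injury worsens, the score still does not move.

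Three things are at stake:

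- **The estimand.** For these patients the primary endpoint follows an injury outside the stage 1–2 target.
- **Power.** Patients held at a high score in both arms shrink the difference between arms and spread the scores. The interim looks for efficacy and futility, at each 25% of enrolment, use the same score.
- **The stage subgroups.** The Discussion promises a treatment-by-baseline-stage interaction and an effect for each stage. A stage I subgroup that contains patients scored 3 or 4 at entry is mislabelled.

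**Working it through.** **Step 1: reproduce the plan's sample size.** Inputs from Sample size considerations: two-sided alpha 0.05 and power 90%, so z = 1.960 + 1.2816 = 3.2415. Table 1 (A), scores 0/I/II/III/IV: intervention 82.5/2.5/12.5/2.5/0, control 72.5/2.5/15/5/5.

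Wilcoxon total N with tie correction: N = z² × (1 − Σp̄³) / [3(θ − 0.5)²]. Here θ is the probability that a control patient scores worse than an intervention patient (ties count half), and p̄ are the category proportions averaged over the arms.

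- θ = 0.55625 and 1 − Σp̄³ = 0.5318.
- N = 10.507 × 0.5318 / (3 × 0.05625²) = 589. A form with separate null and alternative variances gives 584. The plan states 586.
- The plan's interim-adjusted 668, with 10 measurements and ICC 0.8: 668 × (1 + 9 × 0.8)/10 = 547.8, that is 548, as stated.

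The plan's figures therefore reproduce, and they describe only patients starting at stage I or II.

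**Step 2: add a share q with a persistent higher-stage injury.** The documents do not give q, so it is an assumption. I also assume that these patients stay at score III (or IV) throughout in both arms, and that Table 1 (A) holds for everyone else. Each category then becomes (1 − q) × Table 1 (A), with q added to III (or IV). The interim inflation and design effect are left unchanged. With N(q) from the Step 1 formula:

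Power = Φ(3.2415 / √(N(q)/N(0)) − 1.960); N for 90% power = 548 × N(q)/N(0).

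| Held at | q | θ | 1 − Σp̄³ | N(q)/N(0) | Power | N for 90% |
|---|---|---|---|---|---|---|
| III | 5% | 0.5537 | 0.598 | 1.23 | 83% | 675 |
| III | 10% | 0.5512 | 0.656 | 1.49 | 76% | 817 |
| III | 20% | 0.5460 | 0.748 | 2.10 | 61% | 1153 |
| IV | 5% | 0.5520 | 0.598 | 1.32 | 81% | 723 |
| IV | 10% | 0.5478 | 0.657 | 1.71 | 70% | 937 |
| IV | 20% | 0.5400 | 0.750 | 2.79 | 49% | 1528 |

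The other variance form changes power by less than 0.3 percentage points in every row. Shrinking only the effect by (1 − q) gives 87%, 83% and 74%. That understates the loss, because the extra spread of scores (the fourth column) also counts.

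**Step 3: when does the qualifying injury count?** The score is the maximum over injuries at each assessment. The qualifying injury sets it only once the other injury has healed below it or it has overtaken the other. Until then, the other injury alone sets it.

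**The case against.** - **Never counting.** A reader might infer that the qualifying injury never counts for these patients and that their score cannot worsen. The documents do not support that. The score is re-taken at each assessment, so the qualifying injury can come to set it. Only an injury at stage IV has no room to worsen; a stage III injury can move either way.
- **Who is affected.** The enrolment sentence does not say that the higher-stage injuries must be sacral or ischial, and those elsewhere do not enter the score. The exclusion for gluteal skin breakdown may remove some patients. Both points limit the number affected. Neither resolves the conflict, because the same paragraph expressly admits higher-stage patients and refers to one among several sacral or ischial injuries.
- **Response of the other injury.** The mechanism described is regional, so a co-existing stage III sacral injury might also respond to IES. That stands: zero response in Step 2 is an assumption, and the figures are illustrations.
- **Another reading.** The Primary outcome section says the outcome is based on stage 1 and stage 2 ulcers combined, which might mean the worst among injuries that began at those stages. Sample size considerations and the Discussion, however, use this language for pooling the two starting strata, not for choosing which injury is scored.
- **Sample size re-assessment.** The internal pilot revisits control-group proportions and within-subject correlation at the first two interims and may raise N. That could recover power, but it would not change what is scored.
- **Secondary endpoints.** A reader might infer that time to resolution and time to worsening share the flaw. Their definitions are not tied to the worst score, so this holds only if the worst-injury rule is carried over to them.
- **Bias.** A reader might infer bias between arms. Randomization is unaffected and the rule is the same in both arms, so there is no ground for that.

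**Conclusion.** The enrolment rule and the scoring rule conflict as written; this is not a detail left to a fuller document. For patients with a co-existing sacral or ischial injury above stage 2, the score at entry is 3 or 4. That contradicts the stage I/II stratum, the stage 1–2 hypothesis and the starting stages in Table 1, and it lasts for as long as that injury remains the worst.

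The consequence is possible dilution and mislabelled stage I and II subgroups. Its size depends on a share the documents do not give. It is negligible if that share is near zero and material from about 5% under the assumptions of Step 2. Those assumptions are a constant score in both arms, an unchanged design effect, and the plan's Wilcoxon approximation rather than the mixed ordinal model, whose subject random effect the calculation does not represent.

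This should be fixed, but it does not undermine the randomized comparison.

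**What to change.** Reconcile the Trial population, Randomization and blinding, Significance level and Primary outcome sections:

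1. Base the primary score on the worst sacral or ischial injury among those that were stage 1–2 at consent or arose after randomization. Injuries already above stage 2 at consent do not set the score.
2. Assign the stage I/II stratum, and the baseline stage used in subgroup analyses, from the same injury.
3. Keep the worst score over all sacral and ischial injuries as a sensitivity analysis.
4. State that time to resolution and time to worsening follow the same injury or injuries.

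**Cost.** Location and stage are already recorded twice daily, so no new assessment is needed. The work is in mapping records to individual injuries, with a rule for lesions that merge. It must also be done for patients already enrolled (176 as of December 30, 2023). The definition is best settled before further interim looks use the score.

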### Patient recruitment

Study personnel will screen the hospital patient lists in the electronic medical record for nursing-documented or wound care nursing-documented pressure ulcers. Some sites also utilize bedside screening in intensive care units.

### Randomization and blinding

Randomization sequences will be generated using the PLAN procedure in the SAS statistical software and will be stratified by clinical site and initial pressure injury stage at point of consent (stage I or II). Furthermore, random sized blocks will be used. Study personnel will randomize patients after enrollment via a central 24-h Interactive Web Randomization System (REDCap). This is an open label study, so no blinding is required. Randomization codes will be maintained until after all the data are collected and analyzed. The patient and study staff will be informed of the randomized allocation.

### Trial intervention

#### Intermittent electrical stimulation device

The Prelivia System™ is a IES system composed of a simulator (Prelivia, Rehabtronics) and self- adhesive, non-sterile 7.5 by 10 cm surface gel electrodes (Axelgaard Pals Platinum Neurostimulation electrodes, Model 895340-4-40, Fallbrook, CA) applied directly on the skin (Fig. 2).

**Fig. 2 Fig2:**
[figure not shown]
The IES system. Electrodes are placed directly on the skin overlying the gluteal muscles but not directly on the pressure ulcer

The device produces charged pulses at 30 Hz. Stimulation intensity is progressively increased until visible muscle contractions of the gluteus maximus muscles are seen, up to a maximum current of 100 mA. Stimulation occurs for 10 s every 10 min. Chosen device parameters approximate those shown to induce pressure redistribution and sustained elevation in tissue oxygenation based on previous studies. Each subject will receive IES consistently 24 h a day from entry and while in the ICU except for brief periods necessary for particular tasks in patient care (ex. dressing changes, operating room needs). While in non-ICU environments, the device will be used while in bed and not participating in physical therapy, mobilization, toileting, and similar activities where no consistent pressure in applied to the sacral area. The study device will be used until discharge, death, patient or LAR request for disenrollment, or the need for surgical or other interventions that preclude the use of IES. Should patients request not to have the study device for a short period of time, this will be notated and they remain in the trial group. If there are patient concerns about contextual use of the device, such as toileting or sleeping, these are discussed with the patient, and should the patient not have the device on per the protocol, this will be noted in the twice daily assessments. If there are medical interventions that require that the sacrum and ischium not be examined, such as unstable open-chested patients, short-term pausing is acceptable and will be documented on the case report form (Additional file 2). If these interventions are longer term or if the patient develops any condition not conducive to the use of the trial device, the device will be discontinued until these conditions are resolved. Research personnel will visit each subject in the study group Monday through Friday to administer a questionnaire to the bedside nurse, ensure proper use of the device, and address participant concerns.

Subjects in the intervention group will receive all other wound care preventatives and treatments that are standard of care. No standard interventions for wound care treatment are prohibited. The standard of care comparator is to isolate the effect of IES in addition to what is the current standard of care.

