#### Exploratory

Our first exploratory endpoint will be total hospital cost effectiveness analysis within a subset of the patients. We will measure incremental cost-effectiveness ratios (ICERS) between traditional care and IES interventions of each procedure for the treatment of pressure ulcers, done within a subset of the patients. Furthermore, patient experience with respect to sleep disturbance, distraction or discomfort, and feeling of electric shock will be assessed with a daily questionnaire. Daily assessment of the device area with respect to redness or skin issues will similarly be documented with a daily questionnaire (Additional file 3). The assessors will be research personnel.

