#### Exploratory endpoints

We will assess cost effectiveness of IES vs standard care within a subset of the patients studied. We will measure incremental cost-effectiveness ratios (ICERS) between traditional care and IES interventions in the treatment of pressure ulcers. Safety assessment is as follows: results from each of the 5 possible side effects listed on Patient and Assessor Questionnaire will be summarized as (1) proportion of patients ever having the event across their follow-ups, (2) severity grade across follow-ups for those having the event, and (3) severity grade for all patients, assigning a 0 to those without the event. Severity grade will be summarized using median [quartiles] and mean (SD). Confidence intervals within and between randomized groups will be estimated using bootstrap resampling with replacement to account for within-subject correlation across measurements.

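### Side effects are to be assessed daily by research personnel, but research visits are scheduled only Monday to Friday, so brief weekend events may be missed

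*Protocol article*

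**What the plan says.** The Exploratory part of Outcome variables sets a daily frequency twice. For the patient's side: "patient experience with respect to sleep disturbance, distraction or discomfort, and feeling of electric shock will be assessed with a daily questionnaire". For the skin: "Daily assessment of the device area with respect to redness or skin issues will similarly be documented with a daily questionnaire". It then names who does this: "The assessors will be research personnel".

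The section on the intermittent electrical stimulation device describes when those staff attend: "Research personnel will visit each subject in the study group Monday through Friday to administer a questionnaire to the bedside nurse". The same section has the device running around the clock in the ICU apart from short care-related interruptions, and in bed elsewhere. It states no weekend pause.

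The Exploratory endpoints part of the analysis section gives three summaries for each of five side effects on the Patient and Assessor Questionnaire: "proportion of patients ever having the event across their follow-ups"; "severity grade across follow-ups for those having the event"; and "severity grade for all patients, assigning a 0 to those without the event".

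The adverse event section restricts collected adverse events to skin irritation and allergies.

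**The concern.** A site cannot follow both frequency statements with the staffing described. If it follows the weekday schedule, exposure continues at weekends while assessment stops. An event that begins and ends between Friday's and Monday's visits is then recorded only if someone asks about it afterwards, and the article describes no such question.

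This matters most for discomfort, feeling of electric shock and sleep disturbance. Adverse event reporting does not cover them, so the questionnaire is the only planned and summarised source. The Discussion says the side-effect data will help describe the device. A proportion that omits brief weekend events would make the device look somewhat better tolerated than it was.

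**Working it through.** The plan gives no expected rate, sample size or power for the side-effect items, so there is no figure of its own to reproduce.

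**Side by side**

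- Frequency: daily (Exploratory outcomes) against Monday to Friday (device section).
- Staff: research personnel in both places.
- Purpose: experience with the device and skin in the one; a questionnaire, proper device use and participant concerns in the other.
- Respondent: the patient's own experience in the one, the bedside nurse in the other.

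Shared staff and purpose make it likely that both describe one data collection. The article does not say so, and the difference in respondent leaves some doubt.

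**Coverage.** Scheduled days: 5/7 = 71.4%. Unscheduled days: 2/7 = 28.6%.

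**A single episode with a uniformly distributed start day, falling wholly on a weekend**

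- one day long: 2/7
- two days long: 1/7 (Saturday start only)
- three or more days long: 0

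**Stays with no weekday at all.** For a two-day stay, 1/7. For three days or more, none.

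**Proportion of patients ever having the event.** The following are assumptions, not figures from the document: stay L from 2 to 30 days; daily event probability p from 0.02 to 0.20; independent one-day events; no weekend look-back; each start day equally likely.

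- Assessed every day: 1 − (1 − p)^L.
- Assessed on weekdays only: 1 − (1 − p)^w, where w is the number of weekdays in the stay, averaged over the seven start days.

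Seven-day stay, p = 0.05 (w is always 5): 1 − 0.95^7 = 0.302 against 1 − 0.95^5 = 0.226.

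Two-day stay, p = 0.05: daily gives 1 − 0.95^2 = 0.0975. On weekdays only, four start days give two visits, two give one and one gives none: (4 × 0.0975 + 2 × 0.05 + 0)/7 = 0.070.

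| Stay (days) | p per day | Assessed daily | Weekdays only | Ratio |
|---|---|---|---|---|
| 2 | 0.05 | 9.8% | 7.0% | 0.72 |
| 7 | 0.05 | 30.2% | 22.6% | 0.75 |
| 10 | 0.10 | 65.1% | 52.7% | 0.81 |
| 14 | 0.05 | 51.2% | 40.1% | 0.78 |
| 30 | 0.02 | 45.5% | 35.1% | 0.77 |
| 30 | 0.20 | 99.9% | 99.2% | 0.99 |

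Over the assumed range of p, the ratio is 0.72 to 0.73 for two-day stays, 0.73 to 0.85 for seven-day stays and 0.77 to 0.99 for 30-day stays. A long stay therefore removes the loss only if the event recurs; a rare one-day event is still missed at close to the 2/7 rate.

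**The case against.** The strongest reply is that the two places may not describe the same form. The questionnaire in the device section goes to the nurse, while the exploratory outcome concerns the patient's experience. The form itself is in an additional file that is not shown, and it may already ask on Monday about the weekend. This stands as a limit: the conflict is between the two descriptions, and whether data are lost depends on a form that cannot be seen here.

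It is also fair to say that stimulation recurs every 10 minutes, so discomfort or shock may well recur on a weekday. Skin reactions are separately graded and followed as adverse events with no weekday limit stated. Both points stand and reduce the likely loss. The second does not help the other items. The general multiple imputation plan does not clearly help either: a day with no scheduled visit need not create a missing record, and the plan does not say that it applies to this questionnaire.

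A reader might go further and infer that patients who were never asked, or who could not answer because of sedation or consent through a representative, are scored 0. The text does not say this. It gives 0 to patients without the event, which is ordinary for a true non-event, and is silent on patients not assessed. If the nurse is the informant, a patient who cannot speak may still have an assessment. A reader might also multiply 5/7 by an assumed share of 50% to 80% able to self-report and conclude that only 36% to 57% of events are captured. The documents give no such share, and the 5/7 applies only to a single one-day event.

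**Conclusion.** The point holds in a limited form. The daily assessment and the weekday visit schedule conflict as written and need reconciling. If they describe one data collection, 2 of 7 days are unscheduled, and the proportion ever having an event can only be lowered by this. The effect matters for brief events and short stays. It is nil for events of three or more days and small for long stays when events recur. The range of 72% to 99% of the true proportion is an illustration resting on independent one-day events, assumed rates and stays, and no look-back. It is not an estimate for this trial.

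The documents do not support a claim that all side effects, skin reactions included, are certain to be understated. Severity among those having the event has no clear direction of bias. These are exploratory and safety summaries; the primary analysis and sample size are untouched. This is a cheap improvement rather than a serious flaw.

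**What to change.** 1. Make the device section and the Exploratory outcomes section agree on how often, by whom and from whom the questionnaire is completed.
2. If visits stay on weekdays, record Saturday and Sunday as separate dated entries at each Monday visit, from patient or nurse recall and the nursing skin record.
3. In Exploratory endpoints, state that a patient counts as without the event, and scores 0, only if assessed for that item, and show the number assessed beside each summary.

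The cost is two dated entries on the Monday form and a short change of wording. Weekend entries will rest partly on recall, and reported rates may be slightly less favourable to the device. At the date given under Trial progress, 176 patients had been recruited, so 548 − 176 = 372 of the minimum sample (68%) were still to come and could be covered.
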